## Abstract

**Background:**

Combining cyclin-dependent kinases 4 and 6 (CDK4/6) inhibitors with endocrine therapy is an effective strategy to improve progression-free survival in hormone receptor-positive (HR+), human epidermal growth factor receptor 2 (HER2)-negative advanced breast cancer. There is a lack of comparative data to help clinicians decide if CDK4/6 inhibitors can best be added to first- or second-line endocrine therapy. Improvement in median progression-free survival in first-line studies is larger than in second-line studies, but CDK4/6 inhibitors have not consistently shown to improve overall survival or quality of life. They do come with added toxicity and costs, and many patients have lasting disease remission on endocrine therapy alone. No subgroup has been identified to select patients who are most likely to benefit from the addition of CDK4/6 inhibition in any line of treatment. Altogether, these factors make that the optimal strategy for using CDK4/6 inhibitors in clinical practice is unknown.

**Methods:**

The SONIA study is an investigator-initiated, multicenter, randomized phase III study in patients with HR+/HER2-negative advanced breast cancer. Patients are randomly assigned to receive either strategy A (first-line treatment with a non-steroidal aromatase inhibitor combined with CDK4/6 inhibition, followed on progression by fulvestrant) or strategy B (first-line treatment with a non-steroidal aromatase inhibitor, followed on progression by fulvestrant combined with CDK4/6 inhibition). The primary objective is to test whether strategy A is more effective than strategy B. The primary endpoint is time from randomization to second objective progression (PFS2). Secondary endpoints include overall survival, safety, quality of life, and cost-effectiveness. Five-hundred seventy-four events yield 89% power to show that strategy A has statistically significant, clinically meaningful superior PFS2 (according to ESMO-MCBS) in a log-rank test at the two-sided 95% confidence level. Given an accrual period of 42 months and an additional 18 months follow-up, inclusion of 1050 evaluable patients is required.

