### Statistics: Sample size and power calculations

The primary outcome for this study is PFS2, defined as time from randomization to second objective progression. The threshold for a clinically relevant difference in PFS2 is set according to the European Society for Medical Oncology - Magnitude of Clinical Benefit Scale (ESMO-MCBS) [20]. The maximal preliminary score for efficacy based on PFS is 3 out of 4, with a higher score indicating more clinical benefit (see Table 1). The preliminary scores can be upgraded or downgraded depending on data on toxicity and quality of life to achieve the final score.

**Table 1 Tab1:** preliminary magnitude of clinical benefit grade based on PFS

Grade 3	HR ≤0.65 and gain ≥3 months
Grade 2	HR ≤0.65 but gain < 3 months
Grade 1	HR > 0.65

*PFS* progression-free survival, *HR* hazard ratio (thresholds refer to the lower extreme of the 95% confidence interval)

Based on the PALOMA-studies, we estimated strategy A to show a median PFS2 of 31 months and strategy B to show a median PFS2 of 28 months, with a corresponding hazard ratio of 0.85. For strategy A to be preferable according to ESMO-MCBS, a statistically significant difference in PFS of at least three months and a lower limit of the 95% confidence interval ≤ 0.65 for the corresponding hazard ratio is required. In the power calculation we implemented these minimum requirements by multiplying the estimated hazards in the palbociclib + letrozole group (PALOMA-2) and in the palbociclib + fulvestrant group (PALOMA-3) by 0.88 while multiplying the estimated hazards in the letrozole single agent group (PALOMA-2) and fulvestrant single agent group (PALOMA-3) by 1/0.88. This modification of the actual hazards yields expected median PFS2 times of 32.6 and 27.4 months in the strategy A and strategy B, respectively.

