Based on 10,000 simulated trials with the modified hazards we conclude that inclusion of 500 patients per arm in a period of 42 months and an additional 18 months follow-up will yield an expected number of 574 events and 89% power to show that strategy A has statistically significant superior PFS2 in a log-rank test at the two-sided 95% confidence level. The corresponding hazard ratio for strategy A: strategy B is 0.765 (95% CI 0.648–0.902) and the probability of meeting the above-mentioned ESMO-MCBS criteria is 52%. If the study fails to detect superiority, non-inferiority will be tested next. According to the closed test principle, hierarchical testing of superiority and non-inferiority does not affect sample size or power of the analyses.

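### The abstract attaches 89% power to a PFS2 gain that is both significant and ESMO-MCBS clinically meaningful; the sample-size section gives 89% for significance alone and 52% for the ESMO-MCBS criteria

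*Protocol article*

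**What the plan says.** The Methods paragraph of the abstract says: "Five-hundred seventy-four events yield 89% power to show that strategy A has statistically significant, clinically meaningful superior PFS2 (according to ESMO-MCBS"), in a two-sided log-rank test. It gives neither the hazard ratio assumed nor a separate probability for the ESMO-MCBS criteria.

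The section on sample size and power gives the detail:

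- For strategy A to be preferable by ESMO-MCBS, the result must show "a statistically significant difference in PFS of at least three months and a lower limit of the 95% confidence interval ≤ 0.65" for the hazard ratio.
- The effect estimated from the PALOMA studies is a median PFS2 of 31 against 28 months, "with a corresponding hazard ratio of 0.85".
- For the power calculation the hazards were modified by factors of 0.88 and 1/0.88 to build in the ESMO-MCBS minimum, giving medians of 32.6 and 27.4 months.
- Under the modified hazards, 500 patients per arm "will yield an expected number of 574 events and 89% power to show that strategy A has statistically significant superior PFS2". "The corresponding hazard ratio for strategy A: strategy B is 0.765 (95% CI 0.648–0.902").
- Under the same hazards, "the probability of meeting the above-mentioned ESMO-MCBS criteria is 52" per cent.

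**The concern.** The abstract and the sample-size section describe the same design, with the same 574 events, but attach the 89% to different outcomes. In the sample-size section it is the chance of a significant log-rank test. In the abstract it is the chance of a result that is significant and also clinically meaningful by ESMO-MCBS, for which the sample-size section gives 52%.

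The sentence concerns the primary endpoint, stands in the most-read part of the article, and errs in the trial's favour. A reader of the abstract alone would think the trial very likely to show an ESMO-MCBS-level gain if the design effect is true. By the plan's own figures it would miss that criterion about half the time (100% − 52% = 48%). Because the abstract omits both the 0.765 and the 52%, that reader cannot recover the correct statement.

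**Working it through.** **Inputs, all from the sample-size section unless noted.** 574 expected events; two-sided 5% log-rank test; design hazard ratio 0.765 (95% CI 0.648–0.902); ESMO-MCBS limit criterion 0.65; PALOMA-based estimate 0.85. Allocation is 1:1 (Interventions section).

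**Standard error.** SE(log HR) = 2/√574 = 0.0835.

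**Reproducing the 89%.** |ln 0.765| / 0.0835 = 0.2679 / 0.0835 = 3.21. Power = Φ(3.21 − 1.96) = 89.4% (Freedman's formula gives 89.1%). The expected 95% CI is 0.765 × exp(±1.96 × 0.0835) = 0.650 to 0.901, close to the stated 0.648–0.902. The 89% is thus the power for significance alone.

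**Reproducing the 52%.** A lower limit of at most 0.65 needs an observed hazard ratio of at most 0.65 × exp(1.96 × 0.0835) = 0.7655. At a true 0.765 the chance is Φ((ln 0.7655 − ln 0.765)/0.0835) = 50.3%. Using the plan's own interval instead, SE = (ln 0.902 − ln 0.648)/3.92 = 0.0844, and the chance is Φ((ln 0.65 − ln 0.648)/0.0844) = Φ(0.037), about 51%. Both agree with the stated 52% to within two points. The figure is near one half because the modified hazards place the expected lower limit almost exactly on the 0.65 threshold.

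**The joint outcome.** Significance needs an observed hazard ratio below exp(−1.96 × 0.0835) = 0.849. Any observed value at or below 0.7655 is therefore already significant, so requiring significance as well does not lower the 52%; nor can it raise it. The three-month criterion hardly binds: in 3,000 simulated trials under modified hazards, 54.03% met significance and the limit, and 54.0% also met the gain.

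**What 89% for the ESMO-MCBS limit would take.** Φ⁻¹(0.89) = 1.227, so the true hazard ratio would have to be about 0.7655 × exp(−1.227 × 0.0835) = 0.69. The document posits no such value.

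**For the optional disclosure: the same formulas at 0.85.** |ln 0.85| / 0.0835 = 1.947, so power = Φ(1.947 − 1.960) = 49.5%. The expected CI is 0.72 to 1.00, and the chance of a lower limit of at most 0.65 is Φ((ln 0.7655 − ln 0.85)/0.0835) = 10.5%. The number of events by a fixed date may differ under this effect; for 540 to 620 events the ranges are 47–53% and 8–12%.

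**Simulation, as a rough check only.** PFS2 was taken as the sum of two exponential times with the PALOMA medians quoted in the Background, an assumption of this review. Unmodified hazards gave a hazard ratio of 0.845, 53% power and 11.5% for ESMO-MCBS; modified hazards gave 0.759, 91% and 54%. This does not reproduce the plan's model exactly: its medians are 32.0 v 28.8 months (plan: 31 v 28) and 34.3 v 28.5 (plan: 32.6 v 27.4), with 585 events under modified hazards rather than 574. The conclusion rests on the stated figures and the closed forms.

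**The case against.** The best defence is that the abstract's sentence ends by naming a log-rank test, which can deliver only significance. The ESMO-MCBS phrase would then describe the effect for which the trial is powered, in line with the sample-size section, where the minimum requirements were built into the modified hazards. The body prints both 89% and 52%, and no calculation in it is wrong.

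The last point stands, and it limits the finding to wording. The lenient reading does not stand: the abstract speaks of power to show such a result, and the sample-size section defines the ESMO-MCBS requirement on the observed result, with significance, gain and confidence limit. For that result the body's figure is 52%.

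Stronger readings are tempting, and the documents do not support them:

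- **That the trial was wrongly powered because its own estimate is 0.85.** The modification is disclosed, the estimate is kept apart from it, and powering on a target effect is legitimate. No figure in the plan is contradicted by the 49.5% and 10.5%. At 0.85 the expected lower limit is about 0.72, so the plan's own criterion would not usually be met and it owes that effect no high power.
- **That the modified hazards are implausible against the source trials.** Multiplying by 0.88² = 0.774 turns 0.58 into 0.449 and 0.46 into 0.356, against quoted lower limits of 0.46 and 0.36. The second equals its limit at the printed precision, and a target need not be a forecast.
- **That a negative result will be taken by the DSMB as excluding a meaningful gain.** The Safety section gives the DSMB safety monitoring only. What a negative result excludes will depend on the reported confidence interval and the planned non-inferiority test.

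**Conclusion.** The concern holds for the abstract sentence. As worded, it gives 89% to an outcome for which the sample-size section gives 52%, an overstatement of 37 percentage points (89 − 52). This needs no outside source: both figures are stated, for the same simulation and the same modified hazards. The recalculation only confirms the assignment; it assumes 1:1 allocation and approximately proportional hazards, which PFS2 as a sum of two treatment phases does not satisfy exactly, but the agreement within two points shows that this does not matter here.

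The design itself is not in error. The absence of a power figure at 0.85 is a matter of useful disclosure. The point should be fixed, as a wording correction that makes the stated figure less favourable.

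**What to change.** Replace the abstract sentence with wording such as: *574 events give 89% power for a two-sided 5% log-rank test if the hazard ratio is 0.765; the probability of meeting the ESMO-MCBS criteria is then 52%.*

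Optionally, add to the sample-size section that 0.765 is the target effect from the modified hazards, and that at the PALOMA-based estimate of 0.85, 574 events give about 50% power and about a 10% chance of a lower 95% limit at or below 0.65.

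The cost is a change of text. Endpoint, number of events, sample size, test and significance level stay as they are.

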**Discussion:**

This study design represents daily clinical practice, and the results will aid clinicians in deciding when adding CDK4/6 inhibitors to endocrine therapy will benefit their patients most. Additional biomarker analyses may help to optimize patient selection.

**Trial registration:**

http://clinicaltrials.gov: NCT03425838 (8 February 2018). EudraCT-number: 2017–002334-23 (29 September 2017).

**Electronic supplementary material:**

The online version of this article (10.1186/s12885-018-4978-1) contains supplementary material, which is available to authorized users.

## Background

Hormone receptor-positive (HR+), human epidermal growth factor receptor 2 (HER2)-negative breast cancer is the most common subset of breast cancer [1]. About one-third of all HR+/HER2-negative patients, initially diagnosed with early stage disease, experience disease recurrence [2]. As a result, the HR+/HER2-negative subset is responsible for the majority of breast cancer related deaths.

For decades, the mainstay treatment of HR+ advanced breast cancer (ABC) has been sequential endocrine therapies targeting the estrogen receptor-signaling pathway. Although endocrine therapies may lead to durable disease control, the majority of patients progress during endocrine therapy (acquired resistance) and there is also a proportion of patients that fails to respond to initial therapy (de novo resistance) [3].

In an effort to overcome endocrine resistance, treatments with novel molecular targets have been developed, including cyclin-dependent kinase 4 and 6 (CDK4/6) inhibitors. CDK4/6 inhibitors prevent cell cycle progression from G1 into S phase [4]. Several (pre)clinical studies have shown efficacy of combining CDK4/6 inhibitors with endocrine therapies in HR+/HER2-negative ABC [5–9]. Currently, three CDK4/6 inhibitors have been FDA- and EMA-approved: palbociclib, ribociclib, and abemaciclib.

In first-line setting, adding CDK4/6 inhibitors to aromatase inhibitors leads to approximately doubling of progression-free survival (PFS). The PALOMA-2 phase III trial randomized patients between either letrozole and palbociclib or letrozole and placebo. Median PFS in the palbociclib-group was 24.8 months versus 14.5 months in the control group (hazard ratio (HR) 0.58 (95% confidence interval [CI]: 0.46–0.72)) [8]. The MONALEESA-2 trial with ribociclib resulted in a median PFS in the combination group (ribociclib with letrozole) of 25.3 months versus 16.0 months in the control group (placebo with letrozole) with an HR of 0.57 (95% confidence interval [CI]: 0.46–0.70) [10, 12]. In the MONARCH-3 trial, abemaciclib was used. Median PFS was not reached in the combination group (abemaciclib with either letrozole or anastrozole) versus 14.7 months in the control group (placebo with either letrozole or anastrozole), with an HR of 0.54 (95% confidence interval [CI]: 0.41–0.72) [9].

Combining CDK4/6 inhibitors with fulvestrant proved to be an effective strategy in second and subsequent treatment lines. In the PALOMA-3 phase III trial patients whose disease had progressed after one or more previous lines of therapy were treated with either fulvestrant and palbociclib or fulvestrant and placebo. The PFS in the combination group (palbociclib with fulvestrant) was 9.5 months versus 4.6 months in the control group (placebo with fulvestrant) with an HR of 0.46 (95% confidence interval [CI]: 0.36–0.59) [5]. The MONALEESA-3 study compared fulvestrant with or without ribociclib in patients who were treatment naïve or had received up to one line of prior endocrine therapy. Median PFS increased from 12.8 months in the fulvestrant + placebo group to 20.5 months in the fulvestrant + ribociclib group (HR 0.59; 95% confidence interval [CI]: 0.48-0.73) [13]. Combining abemaciclib with fulvestrant as second-line treatment in the MONARCH-2 trial resulted in a median PFS of 16.4 months versus 9.3 months in the control group (placebo with fulvestrant) with an HR of 0.55 (95% confidence interval [CI]: 0.45–0.68) [11]. Different from PALOMA-3, only one prior line of endocrine therapy was allowed and no chemotherapy for metastatic disease was allowed. This probably accounts for the differences in median PFS between both studies. The hazard ratios, however, are very similar.

The above-mentioned studies have led to the firm belief that combining CDK4/6 inhibitors with endocrine therapy leads to an improved PFS in HR+/HER2-negative advanced breast cancer. Remarkably, no benefit in overall survival (OS) could be demonstrated so far. The only available mature OS data at this point arise from the preceding phase II PALOMA-1 trial. In this study, OS was very similar with and without palbociclib [14]. A recently published update of the PALOMA-3 data did not show a statistically significant overall survival benefit for the addition of palbociclib to fulvestrant in the entire trial group [15].

Combining CDK4/6 inhibition with endocrine therapy is associated with increased toxicity compared to endocrine therapy alone [5, 8–11]. Almost 70% of patients experience CTCAE grade 3–4 toxicity with the combination compared to 20% with endocrine therapy alone. Patients treated with combination therapy primarily experience bone marrow suppression, but may also experience fatigue, diarrhea, liver dysfunction, and QTc prolongation. As a result, the use of CDK4/6 inhibitors requires more frequent hospital visits and controls. The average duration of use of CDK4/6 inhibitors is substantially longer in first-line compared to second- or subsequent lines (approximately 25 months and 9–16 months, respectively). This means patients are subjected to potential side effects and more frequent hospital visits for a longer period of time when CDK4/6 inhibitors are used as a first-line treatment. This might be part of the reason why despite the clear benefit in PFS, adding a CDK4/6 inhibitor to endocrine therapy to first-line treatment does not clearly result in improved quality of life (QoL). Health-related QoL, as assessed by validated questionnaires, did not differ between treatment arms in the PALOMA-2 and MONALEESA-2 trial [16, 17]. The effect of CDK4/6 inhibition is consistent across a wide range of subgroups based on clinical and pathological characteristics. As a consequence, no predictive biomarkers exist to select patients who are most likely to benefit from the addition of CDK4/6 inhibition.

In summary, it is currently not known which treatment strategy for deploying CDK4/6 inhibitors will benefit patients most. Adding CDK4/6 inhibitors in first- compared to second-line endocrine treatment may provide longer PFS benefit but is associated with longer use of the drugs, resulting in more toxicity and costs, without clear benefit on OS and QoL [18]. The aim of this project is to evaluate whether the sequence of an AI plus CDK4/6 inhibition in first-line followed by fulvestrant in second-line (strategy A) is superior to the sequence of an AI in first-line followed by fulvestrant plus CDK4/6 inhibition in second-line (strategy B).

## Methods/design

The SONIA study is an investigator-initiated nationwide, multicenter, randomized phase III study in women with HR+/HER2-negative advanced breast cancer who have not received any prior systemic anti-cancer therapy for advanced disease. Patients are randomly assigned to receive either strategy A (first-line treatment with a non-steroidal aromatase inhibitor combined with CDK4/6 inhibition, followed on progression by fulvestrant) or strategy B (first-line treatment with a non-steroidal aromatase inhibitor, followed on progression by fulvestrant combined with CDK4/6 inhibition). A schematic overview of the study design is shown in Fig. 1.

**Fig. 1 Fig1:**
[figure not shown]
Schematic overview of study design. Non-steroidal AI: non-steroidal aromatase-inhibitor, either letrozole or anastrozole (at the discretion of the treating physician). CDK4/6 inhibitor: type of CDK4/6 inhibitor according to physician’s choice and reimbursement policies

### Objectives

The primary objective is to test whether CDK4/6 inhibition added to the non-steroidal aromatase inhibitor in first-line treatment (strategy A) is more effective than addition of CDK4/6 inhibition to fulvestrant in second-line treatment (strategy B). The primary endpoint is progression-free survival after two lines (PFS2), defined as time from randomization until objective disease progression, symptomatic deterioration, or initiation of a new therapeutic agent on second-line treatment, death, or progression during a break in initial therapy and without further therapy within one month, whichever occurs first. When a patient dies while on first-line treatment or is ineligible to continue to second-line endocrine treatment according to protocol, her PFS2 equals her PFS1. Secondary objectives include comparisons of OS, QoL, safety and tolerability, objective response rate (ORR) and cost-effectiveness. Additional biomarker analyses are planned, involving pharmacokinetics and pharmacogenetics analyses as well as baseline, on-treatment and on-progression tumor biopsies, liquid biopsies and nuclear imaging; patients are required to provide additional informed consent for these procedures.

### Inclusion criteria

Eligible patients have histologically or cytologically proven diagnosis of adenocarcinoma of the breast with evidence of locoregional recurrent or metastatic disease and will be candidates to receive non-steroidal AIs as first-line treatment for their advanced disease. Patients are not candidates for curative therapies and may not have received any prior systemic anticancer therapies for metastatic disease other than a maximum of 28 days of palliative endocrine treatment. (Neo)adjuvant aromatase inhibitor use is allowed, provided that the disease did not progress while on or within 12 months from ending treatment. Patients must have measurable or evaluable disease as per RECIST 1.1 [19]. Bone lesions visible on bone scan or fludeoxyglucose positron emission tomography (FDG PET) should be confirmed by computed tomography (CT) or magnetic resonance imaging (MRI) at baseline. The patient or a legal representative must be able and willing to give informed consent.

### Exclusion criteria

Patients are excluded from this study in case of advanced, symptomatic, visceral spread with the risk of life-threatening complications in the short term and in case of known active uncontrolled or symptomatic metastases of the central nervous system (including leptomeningeal disease). Patients who are currently being treated with strong cytochrome P450 3A4 (CYP3A4) inducers or inhibitors or were previously treated with CDK4/6 inhibitors, are not amenable for study participation. Other conditions excluding a patient from participating are other malignancies (except those that are not believed to influence the patient’s prognosis and do not require any further treatment), prolonged QTc time (> 480 ms), bowel disease interfering with the uptake of oral medication, or any other medical condition that interferes with study procedures or compliance.

